## Abstract

**Background::**

Coronary heart disease (CHD) is the leading cause of death globally. Angina pectoris is closely associated with coronary artery insufficiency, which seriously affects the quality of life and work of patients. Hypercholesterolemia and hypertension (HTN) are risk factors for CHD angina pectoris. The correlation between hypercholesterolemia with or without HTN and the severity of coronary arteries has not been clarified.

**Objective::**

To explore the correlation between hypercholesterolemia and the degree of coronary artery stenosis (CAS) of CHD angina pectoris, and to further research the influence of HTN on total cholesterol level and CAS, so as to provide guidance for clinical prevention and treatment.

**Methods::**

A multicenter, retrospective clinical study was conducted in the medical records management system of 6 hospitals in Tianjin. Patients who were suffered from CHD angina pectoris and aged from 35 to 75 years old are involved. They hospitalized in the Department of Cardiology between September 1, 2014, and September 1, 2019, and underwent coronary angiography. We divide patients into 3 groups based on the total cholesterol level, the degree of CAS is evaluated by Gensini score, and further divide them into 6 subgroups based on with or without HTN. Collect and analyze the demographics, laboratory information, clinical outcome data, and coronary angiographic data of patients.

**Conclusion::**

Through clinical research data, the study will help to provide guidance for the prevention and treatment of CHD angina pectoris complicated with diseases and promote further research.

## Introduction

1

Coronary heart disease (CHD) is a heart disease that is caused by myocardial ischemia, hypoxia, or necrosis because of coronary stenosis, or occlusion of coronary atherosclerosis.^[1]^ Angina pectoris is typical in clinical and closely associated with inadequate coronary blood supply; it can seriously affect the life and work of patients and families. Therefore, the prevention and treatment of angina pectoris should be taken into consideration.^[2–4]^ According to a report released in 2017 by the International Cooperation Study on the Global Burden of Disease, CHD is the leading cause of death in all diseases globally, with an estimated 110 million people suffered from CHD and 8.92 million deaths due to CHD, and the prevalence continues to rise.^[1,5]^ Evidence-based medicine and a large number of clinical epidemiological investigations show that hypercholesterolemia and hypertension (HTN) are risk factors for CHD angina pectoris.^[6]^ Hypercholesterolemia has resulted in 4 million deaths and a disability-adjusted life loss of up to 88.7 million people globally.^[7]^ Through multiple studies of risk analysis of CHD angina pectoris, HTN is generally regarded as an important risk factor for CHD angina pectoris.^[8]^ Combined with Gensini scoring system, Coronary angiography (CAG) makes a precise diagnosis of the number, location, scope, and vascular wall of coronary artery stenosis (CAS),^[9]^ CAG is regarded as the best way to diagnose CHD and the most powerful method of evaluating the degree of CAS.^[10]^

According to the report, some scholars have conducted combined studies of hypercholesterolemia and HTN. Still, no studies have reported the influence of HTN on the correlation between hypercholesterolemia and the degree of CAS. Therefore, we conduct a retrospective study to explore the relationship between hypercholesterolemia and CAS and whether its relationship is affected by HTN. Through clinical data, we will provide guidance for the prevention and treatment of CHD angina pectoris complicated with diseases and promote further research.

## Method

2

### Study design

2.1

We carried out a multicenter, retrospective clinical study. The collaborative network of CHD research medical units formed by the research team includes the first affiliated hospital of Tianjin University of traditional Chinese medicine (TCM), the second affiliated hospital of Tianjin University of TCM, Tianjin Nankai Hospital, the affiliated hospital of Tianjin Institute of TCM, Tianjin Chest Hospital and Tianjin Medical University General Hospital. The cases of 1000 patients meeting the diagnostic, inclusion and exclusion criteria were collected through the hospital medical record management system.

### Qualification criteria

2.2

#### 
Diagnostic criteria

2.2.1

(1)Diagnostic criteria for CHD angina pectoris: Based on the guidelines formulated by the American College of Cardiology and the American Heart Association (ACC/AHA) in the Guidelines for the Treatment of Chronic Stable Angina Pectoris (2007) and the Guidelines for the Management of Patients with Unstable Angina Pectoris and Non-ST-Elevation Myocardial Infarction (2011), and referring to the Guidelines for the Diagnosis and Treatment of Chronic Stable Angina Pectoris in China in 2007 and the Guidelines for the Diagnosis and Treatment of Unstable Angina Pectoris and Non-ST-Elevation Myocardial Infarction in China in 2007, and the Standard for the Consensus of Integrative Medicine for Integrative Medicine for the Treatment of CHD (2019).^[11]^

Diagnosis can be given if it meets any 1 or more of the following:

1.There was a clear history of old myocardial infarction.2.Previous CAG or coronary CTA examination showed that at least 1 major branch of the coronary artery has a lumen diameter stenosis ≥ 50%.3.Those with ST-segment depression or T-wave inversion on ECG after coronary revascularization.

CHD unstable angina pectoris includes the following subtypes:

1.Resting angina pectoris: it occurs at rest and usually lasts for more than 20 minutes.2.Initial angina pectoris: it newly occurs within 1 month, which can be manifested as the spontaneous seizure coexists with the labor seizure, and the pain grade is above III.3.Aggravated exertional angina pectoris: it has a previous history, with the worsening of symptoms, frequent attacks, prolonged duration, or lower pain threshold in the last 1 month.4.Variant angina pectoris: it often happens spontaneously. It is characterized by transient ST-segment elevation, most of which relieve spontaneously, only a few develop into myocardial infarction.

(2)Diagnostic criteria of hypercholesterolemia:According to the Expert Consensus on Diagnosis and Treatment of Dyslipidemia with Integrated Traditional Chinese and Western Medicine,^[12]^ hypercholesterolemia is diagnosed when total cholesterol (TC) ≥ 5.18 mmol/L. Based on the TC level, we divide patients into 3 groups: patients with TC < 5.18 mmol/L belong to normal TC (NTC) group, 5.18 ≤ TC < 6.19 mmol/L is borderline-high TC (BHTC) group, those with TC ≥ 6.19 mmol/L belong to high TC (HTC) group.(3)Diagnostic criteria of HTN:If the patients have been diagnosed with HTN or are currently taking antihypertensive drugs, we will classify they as HTN group.^[13]^ Otherwise, we will redefine HTN as systolic blood pressure (BP) ≥ 130 mm Hg or diastolic BP ≥ 80 mm Hg according to the recently published 2017 ACC/AHA guidelines.^[14]^

#### 
Inclusion criteria

2.2.2

1.Patients aged from 35 to 75 years old, male or female.2.Those who were hospitalized between September 1, 2014, and September 1, 2019.3.Those with CHD angina pectoris and have undergone CAG in the inpatient department of internal cardiovascular medicine.4.The diagnosis of hypercholesterolemia, CHD angina pectoris and HTN is accorded with the diagnostic criteria.

#### 
Exclusion criteria

2.2.3

1.Those with other cardiac diseases, gastroesophageal reflux disease, or hiatal hernia, neurosis, spinal, or vertebral artery cervical spondylosis, hyperthyroidism, climacteric syndrome, etc.2.Those with myocarditis, cardiomyopathy, acute myocardial infarction, third degree of heart failure, severe heart valve disease, major diseases such as malignant tumor and serious metabolic diseases, liver failure, or renal failure.3.Those with psychotic disorders or cognitive dysfunction.4.Those of childbearing age and have fertility requirements, pregnant women, or lactating women.5.Those allergic to the iodine contrast medium.6.Those who are not suitable for the study, as judged by the researcher.

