### Observation indicators

2.4

In the hospital medical record management system, we collect the clinical data of the first day of hospitalization of the patients, which include demographics such as age, gender, ethnicity, weight, smoking, medical history, BP; clinical biochemical tests such as fasting plasma glucose, glycated hemoglobin, TC, Triglyceride, high density lipoprotein cholesterol, low density lipoprotein cholesterol, C-reactive protein, Fibrinogen and other indicators; CAG data in imaging examination.

According to the location and degree of the lumen stenosis, the score of the degree of each CAS is calculated. In order to calculate Gensini score (GS), the percentage diameter of the stenosis is assigned based on the severity of the stenosis (from 0–32): 1 point for stenosis ≤ 25%, 2 points for stenosis 26% to 50%, 4 points for stenosis 51% to 75%, 8 points for stenosis 76% to 90%, 16 points for stenosis 91% to 99%, and 32 points for stenosis 100%. Lesion site score: 5 points for left main coronary artery, 2.5 points for proximal left anterior descending (LAD), 1.5 points for middle LAD, 1.0 point for distal LAD, 1.0 point for the first diagonal branch, 0.5 points for the second diagonal branch, 2.5 points for proximal left circumflex (LCX), 1.0 point for distal LCX, 1.0 point for blunt LCX, 1.0 point for posterior descending branch, 0.5 points for posterior branch and 1.0 point for right coronary artery. Multiply the stenosis score by the lesion site score, then add all the scores we will get the final GS, which is defined by 2 independent doctors.^[15,16]^ The data of CAG were separately defined by more than 2 interventional doctors who did not know the rest data of patients, and a third doctor will participate in the analysis if necessary. The GS rule is shown in Table 1.

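### Cholesterol groups ignore lipid-lowering treatment while the hypertension groups count treatment, so treated patients can enter the normal-cholesterol reference group and the TC–Gensini relation may be attenuated

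*Protocol article*

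**What the plan says.** Section 2.2.1, item (2), sets the rule for cholesterol: "hypercholesterolemia is diagnosed when total cholesterol (TC) ≥ 5.18 mmol/L". The grouping follows from the same measurement: "Based on the TC level, we divide patients into 3 groups". The lowest is defined by "patients with TC < 5.18 mmol/L belong to normal TC (NTC) group", the next runs from 5.18 to below 6.19 mmol/L, and the highest starts at 6.19 mmol/L. No clause covers an earlier diagnosis or lipid-lowering drugs.

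Item (3) of the same section sets the rule for hypertension: "If the patients have been diagnosed with HTN or are currently taking antihypertensive drugs, we will classify they as HTN group". Measured pressure decides only for the remaining patients.

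Section 2.4 fixes the time of measurement: "we collect the clinical data of the first day of hospitalization of the patients". TC is among the tests listed. The non-laboratory items are given as "demographics such as age, gender, ethnicity, weight, smoking, medical history, BP". Lipid-lowering treatment is named neither there nor in the exclusion criteria (2.2.3) nor in the statistical methods (2.6.1).

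Section 2.3 crosses the three TC groups with hypertension and takes normal TC without hypertension as the reference.

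**The concern.** The stated objective is the correlation of hypercholesterolaemia with the degree of stenosis, and whether hypertension modifies it. A first-day TC value in a treated patient reflects the drug as well as the disease. For blood pressure the protocol recognises this and lets treatment define the condition. For cholesterol it does not. The six cells therefore cross hypertension by history, treatment or measurement with cholesterol as measured on the day.

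The eligible population makes this relevant. Qualifying evidence of coronary disease includes "There was a clear history of old myocardial infarction", stenosis of at least 50% on previous imaging, and ECG changes after revascularisation. Many such patients will have had known disease before the index admission, when lipid-lowering treatment may already have begun.

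Two effects are possible. Moving treated patients into the lowest TC group dilutes the contrast. If patients with worse disease are also treated more often, the lowest group gains patients with high Gensini scores, and the relation can vanish or change sign. A larger sample removes neither effect.

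**Working it through.** The documents state no figure on this point, so there is nothing to reproduce. The check is what the stated rule does under assumed treatment patterns.

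**Inputs.** From the article: cut-offs 5.18 and 6.19 mmol/L, and 1000 patients. Assumed: untreated TC normal with mean 5.0 to 5.3 and SD 1.0 mmol/L; 40% to 80% treated; TC reduction of 20% to 30%; true correlation of untreated TC with severity 0.20.

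**1. Who moves.** With proportional reduction r, a treated patient is labelled normal TC if untreated TC is below 5.18/(1 − r). That limit is 5.18/0.80 = 6.475 at 20% and 5.18/0.70 = 7.40 at 30%. Both exceed 6.19, so some patients drop from the highest group to the lowest.

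**2. How many, if treatment is independent of TC.** Let p be the treated share, A = P(untreated TC < 5.18) and B = P(untreated TC < 5.18/(1 − r)).

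- Share of truly hypercholesterolaemic patients labelled normal = p(B − A)/(1 − A).
  - Lowest (mean 5.3, p = 0.4, r = 0.20): 0.4 × (0.880 − 0.452)/0.548 = 0.31.
  - Highest (mean 5.0, p = 0.8, r = 0.30): 0.8 × (0.992 − 0.571)/0.429 = 0.78 to 0.79, depending on rounding.
- Share of the normal-TC group that is treated hypercholesterolaemia = p(B − A)/[A + p(B − A)].
  - Lowest (mean 5.0, p = 0.4, r = 0.20): 0.143/0.715 = 0.20.
  - Highest (mean 5.3, p = 0.8, r = 0.30): 0.424/0.876 = 0.48.

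**3. Effect on the correlation, and whether stratifying helps.** Let z be standardised untreated TC. Severity s = 0.2z + √(1 − 0.04)·e. The log-odds of treatment are a + gT·z + gS·s, with a set so that 60% are treated. Mean TC is 5.2, SD 1.0, reduction 25%. Correlations of measured TC with severity (2,000,000 simulated patients per row; the third decimal varies by run):

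| gT | gS | all patients | untreated only | treated only |
|---|---|---|---|---|
| 0 | 0 | 0.160 | 0.200 | 0.200 |
| 0 | 0.5 | 0.022 | 0.195 | 0.195 |
| 0 | 1.0 | −0.086 | 0.183 | 0.183 |
| 1 | 0 | 0.144 | 0.182 | 0.184 |
| 1 | 0.5 | 0.005 | 0.092 | 0.105 |
| 1 | 1.0 | −0.103 | 0.020 | 0.048 |

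In every row both strata lie closer to 0.20 than the pooled value does. In the last two rows they still fall well short, because treatment depends on both TC and severity and selecting on it distorts their relation. With gT = 1, about 5% of untreated patients are in the highest TC group: about 0.047 × 400 = 19 per 1000 before the split by hypertension.

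**4. Other assumptions.** A second simulation used mean 5.2, SD 1.1, 30% to 70% treated and 20% or 30% reduction. Of the normal-TC group, 19% to 45% had untreated TC of at least 5.18. With nobody treated, the highest and lowest groups differ by 0.45 SD of severity.

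- Treatment unrelated to severity: 0.30 to 0.43 SD, correlation 0.13 to 0.18.
- Log-odds 0.5 per SD of severity: 0.16 to −0.14 SD, correlation 0.09 to −0.03.
- Log-odds 1 per SD, 70% treated: −0.08 to −0.55 SD, correlation 0.01 to −0.10.

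The highest TC group shrinks from 18% to between 1.5% and 13% of patients.

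**The case against.** Grouping by measured TC is coherent in itself. Section 2.3 speaks of the correlation between TC and stenosis, and a treated patient at 4.5 mmol/L does have TC below the cut-off. The cut-offs follow one cited source and the hypertension rule another. This stands as far as it goes, but the objective and title speak of hypercholesterolaemia, and a treated value is a poor marker of that.

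The lists in 2.4 are illustrative, medical history is collected and coded (2.5.4), and 2.6.1 allows adjustment for unnamed confounders. The unseen full protocol or case report form may therefore already hold treatment data, and the absence of a field or covariate name is not the point here. The group definition is, and the article states it in full. That it disregards treatment is inferred from the lack of any such clause, made firmer by the hypertension rule beside it.

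A reader might infer three stronger things that the documents do not support:

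- **That the relation is biased to null or reversed as a matter of fact.** Every input is assumed, and reversal needs treatment to be concentrated in severe disease.
- **That all patients had long-known, treated disease.** Section 2.2.1 also lists angina newly arisen within one month, and the previous angiogram or CT has no minimum interval, so newly presenting and untreated patients can qualify.
- **That the primary analysis should be confined to untreated patients.** The last two rows of the table show that this carries selection bias, and it leaves few patients in the highest TC group.

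**Conclusion.** The inconsistency is firm: treatment counts towards hypertension but not towards hypercholesterolaemia. Applying the rule as written places any treated patient with TC below 5.18 mmol/L in the normal-TC group, and in the reference cell if that patient has no hypertension.

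The consequence is a possible bias of unknown size. Attenuation appeared in every assumed scenario with treatment. With treatment unrelated to severity it was moderate, from 0.20 to between 0.13 and 0.18. Near-null or negative values appeared only when treatment was assumed to rise with severity. The treated share, the TC reduction, the TC distribution and the true correlation are all assumptions.

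**What to change.** - **Sections 2.2.1 and 2.4:** extract from the same admission records whether the patient was on lipid-lowering treatment before admission, and whether hypercholesterolaemia had been diagnosed before.
- **Section 2.6.1, main analysis:** include a treatment indicator and a TC × treatment term, and show results separately for untreated and treated patients.
- **Section 2.6.1, prespecified sensitivity analyses:** (a) the comparison in untreated patients only; (b) a grouping that counts prior diagnosis or treatment as hypercholesterolaemia, in line with the hypertension rule. Without a pre-treatment value, treated patients cannot be split between the borderline and high groups, so (b) would be a yes/no grouping.
- **Wording of conclusions:** refer to measured TC given treatment status. A treatment covariate does not restore untreated TC.

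The cost is one or two extra extracted fields, which means a return to the records if extraction is already complete, and smaller cells within strata, with few high-TC patients among the untreated. Selection bias remains in analysis (a), because treatment may depend on both TC and severity, and should be stated when it is reported.

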### Statistical analysis

2.6

Before performing statistical analysis, we shall invite statistical analysts to make plans and specify detailed steps, then carefully examine the data collected. All statistical analysis processes are programmed and archived for future reference.

#### 
Statistical methods

2.6.1

1.Continuous variables conforming to the normal distribution are expressed by standard deviation and mean, and the difference between groups is analyzed by one-way ANOVA.2.If it conforms to non-normal distribution, we use the median, upper quartile (Q1), lower quartile (Q3), 95% confidence interval to express, and rank-sum test (Wilcoxon method) for analysis.3.The classified data are expressed in terms of quantity and percentage and analyzed by the χ^2^ test and Fisher exact probability method.4.If considering the influence of baseline confounding factors, logistic regression analysis is used. The correlation between variables is analyzed by Spearman or Pearson correlation.

We use SPSS version 23.0 (IBM Corporation, Armonk, NY) to conduct all analyses. The general statistical test uses a bilateral test, and bilateral *P* < .05 is considered statistically significant.

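### An exclusion left to the researcher's judgement, and an open-ended exclusion list, allow selection on cholesterol and stenosis jointly in a study of records already complete

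*Protocol article*

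**What the plan says.** All references are to the Protocol article.

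- **Section 2.2.3, exclusion 6:** "Those who are not suitable for the study, as judged by the researcher". No grounds are given, and no record of the reason is required.
- **Section 2.2.3, exclusion 1:** the list of other conditions ends "hyperthyroidism, climacteric syndrome, etc", so it is not closed.
- **Section 2.2.2, inclusion 3:** "Those with CHD angina pectoris and have undergone CAG in the inpatient department of internal cardiovascular medicine". Angiography has been done before a record can qualify. All admissions lie between September 1, 2014 and September 1, 2019.
- **Section 2.4:** "In the hospital medical record management system, we collect the clinical data of the first day of hospitalization of the patients". The items listed include TC, blood pressure and the angiographic data.
- **Section 2.4, blinding:** "The data of CAG were separately defined by more than 2 interventional doctors who did not know the rest data of patients". The article states no other blinding.
- **Section 2.1:** "The cases of 1000 patients meeting the diagnostic, inclusion and exclusion criteria were collected through the hospital medical record management system". How these were chosen among eligible admissions is not stated.
- **Section 2.7:** consent is waived.

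**The concern.** A clause on suitability normally belongs to a prospective trial, where it protects a participant or guards against poor compliance. Neither purpose applies here: the admissions are over, and no treatment or follow-up is planned. Exclusion 5 (contrast allergy) sits oddly beside a condition that angiography was performed. This suggests, without proving it, that the list came from a prospective template.

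The clause does more harm here than in a prospective trial because exposure and outcome both exist when a record is accepted or set aside. The study's only aim is the association of TC, with or without hypertension, with the degree of stenosis. If the decision to set a record aside depends on both, the association among the retained records differs from that among eligible patients. The logistic regression in section 2.6.1 adjusts for baseline confounders. It cannot undo selection that acts through the exposure and the outcome themselves.

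The Discussion also states an expectation, that hypercholesterolemia and hypertension amplify each other. An open judgement clause is least safe where researchers know which pattern is expected.

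**Working it through.** **Stated figure.** The article gives 1000 records with no effect size, standard deviation, power or number eligible, so the figure cannot be reproduced. No stated number depends on this point. What follows is an illustration on assumed rates.

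**Step 1: effect of selection on an odds ratio.** Split records by TC (high or low) and Gensini score (high or low). Let s11, s10, s01 and s00 be the probabilities of being kept, with the first index for TC and the second for the score (1 = high).

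Observed OR = true OR × (s11 × s00)/(s10 × s01).

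- *Exclusion unrelated to both:* all s are equal and the factor is 1.
- *Exclusion on the score alone:* s11 = s01 = a and s10 = s00 = b. The factor is (a × b)/(b × a) = 1.
- *Exclusion of a share e from one discordant cell:* the factor is 1/(1 − e).
- *Exclusion of a share e from both discordant cells:* the factor is 1/(1 − e)².

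| Share e dropped (assumed) | One discordant cell | Both discordant cells |
|---|---|---|
| 5% | 1/0.95 = 1.05 | 1/0.95² = 1.11 |
| 10% | 1/0.90 = 1.11 | 1/0.90² = 1.23 |
| 20% | 1/0.80 = 1.25 | 1/0.80² = 1.56 |

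Only exclusion that depends on TC and score together moves a null odds ratio.

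**Step 2: effect on the planned tests.** Section 2.6.1 specifies "The general statistical test uses a bilateral test, and bilateral" P < .05, with rank-based comparison for non-normal data and Spearman or Pearson correlation. A simulation with no true association used these assumptions, none of them from the article:

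- TC normal with mean 4.65 and SD 1.1 mmol/L;
- Gensini score log-normal and independent of TC, with a high score meaning above the median;
- TC split at 5.18 mmol/L to define discordance;
- a pool of 1600 records, 1000 kept, and 600 runs per setting;
- Spearman correlation, and Kruskal-Wallis across the article's three TC groups.

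| Exclusion pattern | Spearman rejects | Kruskal-Wallis rejects |
|---|---|---|
| Random, or on score alone (5%, 10%, 20%) | 4.0% to 6.7% | 3.7% to 5.5% |
| 5% of discordant records | 8.2% | 7.0% |
| 10% of discordant records | 18.8% | 19.8% |
| 20% of discordant records | 60.2% | 69.7% |

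The simulation standard error at a true 5% is √(0.05 × 0.95/600) = 0.9 percentage points, so the first row is compatible with 5%.

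With the score split at its median and independent of TC, half of all records are discordant. The three drop rates therefore remove 0.5 × 5% = 2.5%, 0.5 × 10% = 5% and 0.5 × 20% = 10% of the pool.

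**Step 3: whether other provisions close the gap.** Blinded angiogram reading protects the score, not entry to the study. Section 2.5.1 provides training, standard operating procedures and audits of the centres. As described, these do not define unsuitability, require a logged reason, or keep the selecting researcher from seeing TC or the angiogram.

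**The case against.** Several stronger readings are tempting, and the document does not support them.

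- **That the 1000 were hand-picked.** Section 2.1 is silent on sampling. This is a condensed article, the full protocol is not shown, and neither is the flow diagram in Figure 1. A consecutive or random rule may exist, so its absence here is not a defect. The two open clauses are different, because they are stated eligibility rules.
- **That the person excluding records sees TC and the angiogram.** Exclusion 6 says only the researcher. That the data lie in one system makes such knowledge possible; it does not document it. The study's Gensini score comes from blinded readers, so a selector might know only the clinical angiogram report.
- **That bias occurred, or that an odds ratio of 1.56 is to be expected.** Nothing indicates that discordant records would be dropped, and no drop rate has a source. At 5% the distortion is modest: 1.11, with rejection of 7% to 8%.
- **That the Discussion's claims are refuted.** It calls the results more representative because several centres contribute. The open clauses weaken its claim of strict criteria without disproving representativeness.
- **That screening could be fully blinded.** Inclusion 4 draws on the TC cut-offs, and the second diagnostic criterion for coronary heart disease in section 2.2.1 is a previous finding of stenosis of at least 50%. Eligibility itself needs some of this information.

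These limits stand. What remains is that exclusion 6 and the open end of exclusion 1 are printed as rules, serve no evident purpose in a record study, and are not constrained by anything shown.

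**Conclusion.** The point holds in a limited form. As written, two exclusion clauses leave entry open to discretion in a study where exposure and outcome predate selection and only the angiogram readers are blinded. This allows selection on TC or hypertension and stenosis jointly; it does not establish it.

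The size of any bias is unknown. The odds ratios of 1.11 to 1.56 rest on assumed loss of 5% to 20% from both discordant cells, and the rejection rates also rest on the assumed distributions. Exclusions unrelated to TC and score jointly would leave the null result intact. The change is worth making because it is cheap and removes a source of bias that the analysis cannot repair.

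**What to change.** 1. Delete exclusion 6 and the open end of exclusion 1, or replace them with a closed list of reasons that can be verified in the record.
2. Log each exclusion with a coded reason, and report exclusions by TC group and centre.
3. If the full protocol does not already set a rule for choosing the 1000, take consecutive or randomly drawn eligible admissions from each hospital's angiography list.
4. Where feasible, decide the exclusions that need neither lipid nor angiographic data before looking at the TC value and the index angiogram result.

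**Cost.** Protocol wording, an exclusion log and, if item 3 applies, a record list per hospital; no extra patients. Abstractors lose discretion over odd records. Section 2.1 speaks of collection in the past tense; if records are already in hand, some re-screening is needed, starting with those excluded under item 6 or the open end of item 1.
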